Consistently, findings of the emotional Stroop test showed higher response latencies for social threat words compared with neutral words, suggesting an impaired ability to disengage attention from threat in SAD [23-26]. Results of the dot-probe paradigm are more mixed. Studies differ in the type of stimulus (words vs. faces) and the length of stimulus presentation (80 ms, 200 ms, 500 ms, >1000 ms). In this paradigm, two stimuli (for example, one neutral and one social threat word) are simultaneously displayed on a computer screen followed by a probe in the location of one of the stimuli. Faster responses to probes in the location of the social threat word compared with responses to neutral words indicate a biased attention towards threat. Faster responses to the neutral cue indicate a biased attention away from threat (avoidance of threat cues). Taken together, results of dot-probe studies suggest that there is some evidence of an attention bias towards threat early in cue detection (≤500 ms) but no attention bias at longer presentation times [27-30]. Fewer studies suggest that there may be an attention bias away from threat [31,32]. This is supported by an eye-tracking study revealing initial and sustained attentional avoidance of social threat faces [33].

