The stimuli will consist of images from 62 men and 62 women, each showing three different facial expressions: positive (happiness), neutral, and negative (disgust), as well as of 111 positive words, 111 neutral words, and 111 negative words. Both the faces and the words are centered on the screen with the faces 4 pixels and the words 180 pixels apart. The stimuli material will be taken from the Umeå University Database of Facial Expressions [61], the Karolinska Directed Emotional Faces [62] and the Matsumoto and Ekman’s Japanese and Caucasian Facial Expressions of Emotion [63].

In the treatment condition, the probe will always be at the same location as the more negative stimulus in the pair. In contrast, in the placebo condition the probe appears randomly, with equal frequency in the two positions. The intervention will consist of 14 sessions of either treatment or placebo exercises. As shown in Table 1, each session will encompass 192 trials.

**Table 1 T1:** Number of trials per probe position per session depending on condition including assessment phase

	**Trials per session**	**Length of stimulus display, ms**	**positive - ****neutral**	**positive - ****negative**	**neutral - ****negative**	**positive****- neutral**	**positive****- negative**	**neutral****- negative**
**Bias assessment**	96	500 (faces)	8	8	8	8	8	8
		500 (words)	8	8	8	8	8	8
**Control training**	192	500 (faces)	8	8	8	8	8	8
		500 (words)	8	8	8	8	8	8
		1000 (faces)	8	8	8	8	8	8
		1000 (words)	8	8	8	8	8	8
**Attention training**	192	500 (faces)	16	16	16	-	-	-
		500 (words)	16	16	16	-	-	-
		1000 (faces)	16	16	16	-	-	-
		1000 (words)	16	16	16	-	-	-

Underlined words indicate the position of the probe.

The attention bias will be assessed in two additional sessions, one before (day 0) and one after (day 15) the training. The attention-bias assessment includes 96 dot-probe trials similar to those of the training sessions, with the cue presented for 500 ms. The probe will appear with equal frequency at the location of neutral, negative, and positive cues (see Table 1).

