### Statistical analysis

All analyses of primary and secondary outcome measures will be conducted as intention-to-treat analyses (ITT). Depending on the amount of drop-out, the ITT analyses will be carried out either as mixed models or using the ‘last observation carried forward’ method. Social anxiety measures will be integrated in a social anxiety composite following the procedure recommended by Rosnow and Rosenthal [65] and applied by Clark *et al.*[66]. The composite score will be generated by converting each social phobia scale across all assessment points to *z*-scores, and then by averaging across the measures. Between-group changes at post-treatment and at 4-month follow-up on the social anxiety composite and on secondary outcome measures will be calculated using analysis of covariance (ANCOVA), with pre-treatment scores as the covariate. Effect sizes between and within the two groups will be calculated with Cohen’s *d* computed with the pooled standard deviation.

Clinically significant change at post- and follow-up assessment will be estimated for the LSAS-SR, the SIAS, and the SPS. In accordance with Jacobson and Truax [67], we will calculate the proportion of improved and recovered participants using the Reliable Change Index and cut-off scores based on the Jacobson and Truax’s formula, *c*.

The attention-bias assessment will produce reaction times for each participant to three kinds of negatively cued trial (positive–negative, neutral-negative, positive-neutral) and to three kinds of positively cued trial (positive–negative, neutral-negative, positive-neutral). We will calculate the mean reaction time for each participant for positively cued and negatively cued trials, eliminating response latencies for inaccurate trials and response latencies less than 200 ms or greater than 2000 ms. To examine changes in attention bias, we will conduct a 2 (pre-assessment/post-assessment) × 2 (attention training/control condition) × 2 (positive/negative) analysis of variance (ANOVA). Furthermore, we will analyze changes in the attention bias from pre- to post-assessment on an individual level using an attention bias score. We will calculate this bias score by subtracting the mean reaction times to negative cues from the mean reaction times to positive cues. Positive individual bias scores will indicate biased attention towards threat. Negative bias scores will indicate biased attention away from threat.

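### The attention-bias score and its ANOVA include positive-neutral pairs, which show no threat stimulus, yet the result is read as bias towards or away from threat

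*Protocol article*

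**What the plan says.** The Statistical analysis section of the protocol article sorts the assessment trials into two classes. There are "three kinds of negatively cued trial (positive–negative, neutral-negative, positive-neutral") and "three kinds of positively cued trial (positive–negative, neutral-negative, positive-neutral"). It then averages within each class: "We will calculate the mean reaction time for each participant for positively cued and negatively cued trials". The only trials removed are inaccurate responses and latencies below 200 ms or above 2000 ms.

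The individual score follows: "We will calculate this bias score by subtracting the mean reaction times to negative cues from the mean reaction times to positive cues". Its reading is fixed as "Positive individual bias scores will indicate biased attention towards threat", and a negative score is read as bias away from threat. The group-level test is a 2 (time) × 2 (arm) × 2 (positive/negative cue) ANOVA, with no factor for pair type.

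The section on attention training and control training sets the active contingency: "the probe will always be at the same location as the more negative stimulus in the pair". In a positive-neutral pair, that stimulus is the neutral one.

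**The concern.** A positive-neutral pair has no threat on screen. Its negatively cued trial is one in which the probe replaces a neutral stimulus. Likewise, in a neutral-negative pair the positively cued trial has its probe at the neutral stimulus. Neutral-stimulus probes thus fall on both sides of the subtraction, and part of the score is a neutral-versus-positive contrast carrying a threat label.

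The training is meant to reduce avoidance of threat cues, and this task is the only attention measure the article describes. Its job is to show whether training moved attention to threat. As written, a shift from positive to neutral stimuli can be reported as a shift towards threat, and a change confined to threat pairs is averaged with trials that cannot show it. The active arm alone receives a consistent contingency on positive-neutral pairs, so such a shift is a realistic possibility.

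**Working it through.** **Inputs.** Table 1, bias assessment: 8 trials per pair type, probe position and stimulus type (faces, words), all at 500 ms. Table 1, attention training: 16 trials per pair type in each of four display blocks. The scoring rule is the one in the Statistical analysis section.

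**The plan's own counts reproduce.**
- Assessment: 3 pair types × 2 probe positions × 2 stimulus types × 8 = 96.
- Training session: 3 pair types × 4 blocks × 16 = 192.

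**Trials without a threat stimulus.**
- Assessment: 2 positions × 2 stimulus types × 8 = 32 of 96, one third. Each cue class has 48 trials, of which 16 come from positive-neutral pairs.
- Training: 4 × 16 = 64 of 192 trials per session, again one third.

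| Pair type | Probe when coded negative | Probe when coded positive | Trials per class |
|---|---|---|---|
| positive-negative | negative | positive | 16 |
| neutral-negative | negative | neutral | 16 |
| positive-neutral | neutral | positive | 16 |

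**What the score estimates.** For each pair type let B be the mean reaction time with the probe at the less negative stimulus minus that with the probe at the more negative one. With equal cells (before errors and latency exclusions),

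score = (B_pos-neg + B_neu-neg + B_pos-neu) / 3.

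Write T for the average of the two threat-containing types and P for B_pos-neu. Then score = (2T + P)/3, and score − T = (P − T)/3. The same holds for a between-arm difference in change.

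**Illustrations (assumed values, not from the article).**

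| T (ms) | P (ms) | Pooled score (ms) |
|---|---|---|
| 30 | 30 | 30 |
| 30 | 0 | 20 |
| 0 | 30 | 10 |
| −10 | 30 | 3.3 |

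The last row shows a person biased away from threat who would be classed as biased towards it.

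**Precision, assuming independent trial noise only.** Signal-to-noise is proportional to the mean effect times the square root of the number of trials.
- No effect in positive-neutral pairs: pooled (2/3) × √96 = 6.53; threat pairs only √64 = 8.00. The threat-only score is better by 8.00/6.53 = 1.22.
- Equal effect in all pairs: 64 trials give √(64/96) = 0.816 of the pooled value, an 18% loss. The 32 neutral-negative trials give √(32/96) = 0.577, a 42% loss.
- Break-even between 64 and 96 trials: if the effect in positive-neutral pairs is a fraction r of that in threat pairs, (2 + r)/3 = 0.816, so r = 0.45. Above that the pooled score is the more precise, though it still does not measure threat bias unless r = 1.

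**The case against.** The best defence is that the score mirrors the intervention. Training is defined by the more negative member of each pair and delivered equally over all three pair types, so contrasting more with less negative stimuli over the same pairs is a coherent check of what was trained. Randomisation is intact, and the pooling does not inflate type I error for a training effect on relative valence. That stands, but it defends a different construct. The article does not call the result a preference for the more negative stimulus; it calls it bias towards threat.

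Three stronger readings are tempting and are not supported.

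- A reader might infer that the plan loses a third of its effect, or that the fix gains 22% in signal-to-noise. Both figures need a zero effect in positive-neutral pairs, although the active arm is trained on those pairs. With equal effects there is no dilution and pooling is the more precise. The ratios also ignore between-person variation in true bias, for which the article gives no figure.
- A reader might infer that the score breaks the trial's own definition of threat bias, because the Background says: "Faster responses to probes in the location of the social threat word compared with responses to neutral words indicate a biased attention towards threat". That sentence describes the dot-probe paradigm in earlier work, with one word pairing given as an example. It shows how the term is generally understood; it does not define this trial's score.
- A reader might infer that the trial's conclusion is at risk. Attention bias is neither the primary nor a named secondary outcome, no mediation analysis is described, and the sample size does not use it.

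Nor is this a detail that a condensed article leaves to a fuller plan: the pooling and the interpretation are both written out. The underlining lost from Table 1 marks only the probe position.

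**Conclusion.** The point holds as a mismatch between the score and its stated meaning. One third of the trials in the score and in the ANOVA's cue factor (32 of 96) show no threat, so the result equals threat bias only if positive-neutral pairs behave like the threat-containing pairs. Otherwise it is off by one third of the difference, in either direction, and the sign of an individual score can be wrong. How far off cannot be said from the article. The counts are certain; the one-third weighting assumes equal cells after exclusions.

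The consequence is confined to the check that training changed attention to threat, at group and individual level. The social anxiety composite, the secondary outcomes and N = 128 are unaffected. It is worth correcting because the attention result will be used to interpret the clinical one, and the correction is nearly free.

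**What to change.** - Name one main threat index before analysis: the 64 trials in neutral-negative and positive-negative pairs. Use it for the 2 × 2 × 2 ANOVA and for the individual scores that are read as towards or away from threat.
- Report as supportive, and separately, the neutral-negative pairs alone (32 trials) and the positive-neutral pairs (32 trials). The neutral-negative pairs are the cleanest threat contrast, since a shift in a positive-negative pair may also reflect attention away from the positive stimulus. They are less precise, which is why they are not proposed as the main index.
- If the pooled 96-trial score is kept as a check of the trained contingency, describe it as bias towards the more negative stimulus and drop the threat wording.

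The cost is a change to the scoring and the text. The task, the data and the assessment schedule stay as they are. The statistical price, if effects are equal in all pair types and trial noise is independent, is about 18% lower signal-to-noise with 64 trials and 42% lower with 32. Naming one main index in advance avoids a choice among several after the data are seen.

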## Discussion

The planned study aims at evaluating the combination of an attention modification training program with an established Internet-based CBT self-help program. Cognitive bias modification programs are theoretically well suited for integration in CBT. Biases in interpretation and attention processes are part of the cognitive model of SAD [21,68]. This model of maintenance is, at the same time, a model of change. All factors of the model are potential starting points of change and most of them are explicitly addressed in CBT. However, so far, the attentional avoidance of external threat cues has not been integrated in CBT manuals. This is certainly due to the implicit nature of this particular maintaining factor. Individuals are hard put to modify their allocation of attention consciously. At this point, the computerized attention training applied in this study offers a very straightforward opportunity to account for the attention bias.

On the other hand, trials on computerized attention training have not yet aimed at integrating them into standard CBT. This may be because bias modification programs were primarily developed to prove the causal relationship of cognitive biases and psychological symptoms [69]. They were not at first designed to treat patients suffering from these symptoms. Only recently has interest in their therapeutic potential arisen and first studies evaluated their efficacy as stand-alone intervention. The findings of this research design will provide an important further step towards an understanding of the potential of CBM. The design also offers a pathway to address, for the first time, an integral part of the cognitive model, not yet covered by CBT manuals, in its interaction with other maintaining factors, such as self-focused attention and safety behaviors.

Our study aims to compare two groups. In addition to the CBT self-help program, one group will receive attention-training exercises, while the other group will receive control training exercises. This randomized add-on design will allow us to draw conclusions about the specific efficacy of ICBT plus attention training compared with ICBT plus control training. It will not, however, allow us to estimate the efficacy of the addition of *any* training compared to *no* training. This comparison would require the inclusion of an additional group receiving ICBT alone. As this would lead to a substantial increase in the required sample size and the required therapist time, we had to decide against it. This is certainly a limitation of our study, which can only partly be addressed by the comparison of the achieved effect sizes with those of previous trials on the ICBT program.

Another limitation of the current design is that the efficacy of the applied attention training as stand-alone intervention has only been demonstrated in one prior study (Carlbring *et al*., in preparation). Prior research has focused on attention-training programs that facilitate disengagement from threat. However, as the training program suggested by Amir *et al*. [34] has not proven efficacious in the Internet-based setting in two randomized controlled trials, we decided to opt for the training protocol that actually produced positive results for participants in a previous Internet-based trial. Based on these tentative empirical data and the strong theoretical basis, we hypothesize that the integration of attention training into the CBT rationale will have a beneficial effect. If the combination of ICBT and attention training will prove successful in the planned study and following replications, the implication would clearly be to aim at integrating attention-bias exercises into ICBT as well as into face-to-face therapies. The standardized and computerized nature of the attention-bias exercises would allow the realization of this implication with little difficulty.

### Trial status

Participant recruitment began on 1 August 2012.

## Abbreviations

ANCOVA: Analysis of covariance; ANOVA: Analysis of variance; CBM: Cognitive bias modification; CBT: Cognitive-behavior therapy; DSM-IV: *Diagnostic and Statistical Manual of Mental Disorders*, 4th edition; ICBT: Internet-biased cognitive-behavioral therapy; ITT: Intention-to-treat; JACFEE: Japanese and Caucasian Facial Expressions of Emotion; LSAS-SR: Liebowtiz Social Anxiety Scale-Self-Report; MADRS-S: Montgomery Åsberg Rating Scale-Self-rated; SAD: Social anxiety disorder; SIAS: Social Interaction Anxiety Scale; SPS: Social Phobia Scale.
